# Constraint-Induced Movement Therapy With or Without Neuromuscular Electrical Stimulation Versus Conventional Therapy for Upper Extremity Function in Chronic Stroke Survivors: Protocol for a Cluster Randomized Controlled Trial

**DOI:** 10.2196/68340

**Published:** 2025-08-28

**Keywords:** stroke, upper extremity, constraint-induced movement therapy, neuromuscular electrical stimulation, Post-stroke, stroke rehabilitation

## Abstract

**Background:**

Motor impairment is a common consequence of stroke, significantly impacting patients’ daily functioning and quality of life. More than 80% of stroke survivors experience upper extremity (UE) motor impairments, which severely impact their ability to carry out daily living activities. Combining motor rehabilitation techniques, such as constraint-induced movement therapy (CIMT), with sensorimotor stimulation methods, such as neuromuscular electrical stimulation (NMES), may be beneficial in enhancing UE functional recovery after a stroke. This combined approach could activate a broader range of brain regions, improving motor control. However, evidence for the effectiveness of these interventions when combined is still lacking.

**Objective:**

In this randomized controlled trial, we aim to determine the effectiveness of CIMT combined with NMES, CIMT alone, and conventional therapy in rehabilitating UE function in chronic stroke survivors.

**Methods:**

We will compare 3 intervention groups, 2 experimental groups (CIMT combined with NMES group and CIMT group) and 1 control group (conventional therapy), in this assessor-blinded, cluster randomized controlled trial. A total of 42 participants will be recruited and randomly assigned to 1 of the 3 groups. Participants in the CIMT group will undergo 6 shaping practice tasks (50 repetitions for each task, totaling 300 repetitions per session). The combined CIMT/NMES group will perform tasks similar to those carried out by the CIMT-only group, and a biofeedback electrical stimulator for NMES will also be provided. The control group will receive conventional neurodevelopmental therapy. All groups will receive 1 session per day of treatment for 3 consecutive days a week for 4 weeks. A blinded assessor will measure the interventions’ outcomes using standardized tests, including UE motor function, motor impairment, perceived motor function, and upper limb self-efficacy. All data will be analyzed descriptively, presenting the means and SDs. We will conduct inferential tests using a 2-way mixed ANOVA to evaluate the effects of the interventions and compare them between and within groups.

**Results:**

Funding for this study was provided by the Research and Ethics Committee of the Universiti Kebangsaan Malaysia (the National University of Malaysia) starting in November 2023. Between January 2023 and May 2023, we developed the initial ethics proposal and recruited research staff. Research ethics applications were submitted to the Research and Ethics Committee of the Universiti Kebangsaan Malaysia from May 2023 to November 2023. We anticipate publishing the study results in September 2025.

**Conclusions:**

This trial will provide insights into the effectiveness of CIMT combined with NMES, CIMT alone, and conventional therapy for UE rehabilitation in stroke survivors. Findings will be published in a peer-reviewed journal, and any updates based on emerging evidence will be provided. Any changes to the study methods will be documented in the final publication.

**Trial Registration:**

Australian New Zealand Clinical Trials Registry ACTRN12624000564550; https://www.anzctr.org.au/Trial/Registration/TrialReview.aspx?id=387308

## Introduction

### Background

Stroke is one of the most debilitating brain disorders, often leading to death or severe functional impairment. The global burden of stroke is exceptionally high in low- and middle-income countries, where increased incidence, mortality, disability, and economic strain are prevalent [1]. Stroke is the second leading cause of death and disability worldwide [2], with over 116 million healthy years lost annually due to disabilities and fatalities associated with stroke [3]. Among stroke survivors, more than 80% experience motor impairments in the upper extremities (UEs) [4], significantly limiting their ability to engage in social and daily activities. While approximately two-thirds of patients who have experienced a stroke can walk independently 6 months after the stroke, nearly half remain unable to functionally use the affected arm despite receiving treatment [5].

UE impairment is a common challenge for stroke survivors, often leading to significant motor dysfunction and impacting daily living activities [6,7]. Improving UE function through targeted rehabilitation is essential for enabling stroke survivors to perform daily tasks independently [8,9]. Constraint-induced movement therapy (CIMT) is a highly effective intervention for enhancing UE function after stroke [10] and is considered one of the most essential rehabilitation approaches for stroke recovery [11]. Numerous systematic reviews provide strong evidence supporting CIMT’s use across acute, subacute, and chronic phases of stroke rehabilitation [12-15]. Consequently, CIMT is recommended as a core intervention in clinical guidelines worldwide, including in the United Kingdom [16], Australia [16], and Canada [17]. In addition, research indicates that CIMT can enhance functional performance compared to traditional rehabilitation and increase the use of the most affected UE [18].

Despite the prevalence of motor impairments following a stroke, neuromuscular electrical stimulation (NMES) interventions are designed to enhance the quality of life and motor function by contracting weak muscles in the affected extremity. This approach aims to address paresis, restore fractionated movements, improve coordination and joint control, and decrease abnormal movement patterns, such as reduced spasticity and abnormal muscle synergies [19]. Clinical evidence supports the therapeutic efficacy of NMES as a complementary approach to traditional physiotherapy. Specifically, NMES for finger, arm, and wrist extension has shown the most significant clinical and neuroprosthetic benefits. Research indicates that individuals with moderate impairments within 2 years after a stroke experience essential improvements in UE function from NMES, especially when the stimulation is synchronized with the individual’s movement intent [19,20].

Motor function recovery is a critical aspect of stroke rehabilitation. However, in the chronic stage of stroke, the pace of functional recovery often slows considerably. This slow recovery rate, combined with the inherent tendency of humans to rely on bilateral arm coordination for functional activities, may lead to the development of compensatory movement strategies that hinder optimal recovery of the affected UEs. Humans instinctively use both arms in a coordinated fashion to carry out daily tasks. Following a stroke, this natural inclination to rely on bilateral arm coordination, coupled with the slow recovery of the affected arm, may lead patients to develop compensatory movements. While enabling individuals to cope with their impairments, these strategies limit the potential for optimal recovery of the affected UE. As patients become increasingly reliant on compensatory movements, they may fail to engage the impaired limb effectively, leading to a plateau in functional improvement. Consequently, rehabilitation professionals must recognize and address these compensatory strategies to promote optimal recovery and prevent long-term functional limitations in chronic stroke survivors. To overcome the challenges posed by compensatory strategies and promote recovery in the chronic stage of stroke, a combined approach integrating motor rehabilitation techniques, such as CIMT, with sensorimotor stimulation methods, such as NMES, may be beneficial [21]. Combined therapeutic interventions demonstrate significant potential for activating diverse brain regions involved in motor control, enhancing recovery following stroke. The clinical implications of these findings suggest that implementing multimodal interventions is essential for optimizing motor recovery in chronic stroke survivors. This approach is substantiated by functional magnetic resonance imaging studies revealing neuroplastic changes associated with combined therapy modalities, demonstrating enhanced cortical reorganization when peripheral stimulation is paired with intensive motor training [21-23]. The neuroimaging evidence provides a neurophysiological basis for the efficacy of combined interventions, offering valuable insights into evidence-based rehabilitation protocols that may inform clinical practice guidelines and future research directions in UE rehabilitation after stroke.

### Objectives

Although CIMT is an established intervention for stroke recovery, limited research exists on the synergistic effects of combining it with NMES. No clinical studies have reported the effectiveness of CIMT combined with NMES in comparison to CIMT alone or conventional therapy for treating UE dysfunction in patients who have experienced a stroke. Therefore, we aim to combine CIMT with NMES to explore the effect of their combination on UE dysfunction in chronic stroke survivors and compare it to CIMT alone and conventional therapy.

## Methods

### Trial Design and Setting

This study is an assessor-blinded, cluster, randomized controlled trial (RCT) comparing 3 intervention groups: 2 experimental groups (CIMT combined with NMES and CIMT alone) and 1 control group (conventional therapy). The trial will be conducted across 3 National Stroke Association of Malaysia (NASAM) rehabilitation centers. NASAM, a primary referral center for stroke survivors in Malaysia, operates 8 centers nationwide, providing rehabilitation services, peer support, and information to stroke survivors.

The study will be reported according to the CONSORT (Consolidated Standards of Reporting Trials) guidelines. The trial schedule is presented in Figure 1, while the trial design flowchart is provided in Figure 2. In addition, the study has been registered prospectively with the Australian New Zealand Clinical Trials Registry under registration number ACTRN12624000564550.

**Figure 1 figure1:**
[figure not shown]
Flow diagram of the study. CIMT: constraint-induced movement therapy; FMA-UE: Fugl-Meyer Assessment for upper extremity; MAL: Motor Activity Log; NMES: neuromuscular electrical stimulation; UPSET: Upper Limb Self-Efficacy Test; WMFT: Wolf Motor Function Test.

### Study Participants

The principal researcher will recruit eligible participants using the predefined inclusion and exclusion criteria, as described in Textbox 1 [24-28].

Inclusion and exclusion criteria.
**Inclusion criteria**
Adults aged 18 to 80 years, with a diagnosis of ischemic or hemorrhagic stroke in the chronic phase (≥6 months after stroke)A score of ≥3 on the upper arm item of the Motor Assessment ScaleA score of ≥44 on the Fugl-Meyer Assessment for upper extremity, with ≥10° active wrist extension and ≥10° active extension of thumb and additional digitsA score of ≥26 on the Montreal Cognitive Assessment [24]. The patients must not have severe impairments in cognitive function, as they should understand the instructions and communicateA grade of ≤2 on the Modified Ashworth Scale for the upper extremity and lower extremity [25]No history of upper extremity injuries. History of upper injuries, such as a fracture or any deformity that can prevent patients from practicing massed tasks with the affected limb
**Exclusion criteria**
Sensory loss score of ≥2 on the National Institutes of Health Stroke Scale sensory item. Such impairments can affect the ability to use the upper extremity in everyday activities [26]Patients with pacemakers or tumors owing to their contraindication to the implementation of the neuromuscular electrical stimulation [27,28]

### Recruitment and Randomization

Participants will be recruited from the NASAM. Three NASAM centers will be randomly assigned to 1 of 3 groups: the CIMT combined with the NMES group, the CIMT-only group, or the control group. Due to the specific nature of the therapies and the distinct characteristics of the centers, randomizing individual participants within centers is impractical. A cluster randomization approach will be used to minimize contamination among patients attending the same center. In addition, to minimize the risk of contamination between intervention groups, a cluster randomization approach will be used, wherein health care centers will serve as the unit of randomization. Each participating center will be randomly allocated to 1 of the 3 intervention arms using a computer-generated sequence administered by research personnel not involved in intervention delivery or outcome assessment. This concealed allocation process ensures allocation concealment and methodological rigor. Following randomization, all eligible patients who have experienced a stroke attending a given center will receive only the intervention protocol assigned to that facility. This methodological approach enables consistent intervention delivery within each site while substantially reducing the likelihood of cross-contamination between intervention groups—a critical consideration when evaluating health care provider–delivered rehabilitation protocols with behavioral components.

Eligible participants will provide written informed consent before their involvement in the study. The principal investigator or a trained research staff member not involved in therapy delivery will be responsible for obtaining consent from each participant. This process will take place only after participants have received a comprehensive explanation of the study procedures, ensuring that they clearly understand their involvement and the associated risks and benefits.

Following the informed consent process, baseline demographic information, including the participants’ names, ages, and gender, will be collected. Once demographic data have been obtained, the remaining baseline assessments will be conducted. Throughout the study, the confidentiality of all participants’ personal information and data will be strictly maintained in accordance with established research ethics guidelines and data protection regulations.

### Blinding

Outcome assessors will be blinded to the group assignments to ensure an unbiased evaluation of the results. However, given the significant differences in the therapies and the nature of the interventions, it is not feasible to blind the therapists or the patients involved in the study. Clinical staff must be aware of the specific therapy they are administering. Therapists will be informed that a study is being conducted on different modalities in other NASAM centers, but no particular details about the treatment regimens or locations will be provided. They will be aware of the treatment regime at their center but are reminded not to disclose this information to other therapists, either within or at different centers.

### Therapist Training and Standardization

Recognizing that therapist-related variability represents a significant potential source of bias in rehabilitation trials, we have developed comprehensive standardization procedures to minimize therapist-level confounding. While the complete elimination of therapist effects remains impossible in hands-on interventions, our multifaceted approach ensures maximum consistency across sites and health care providers.

All participating therapists must complete a 3-day training program before commencing study treatments. This standardized curriculum encompasses theoretical foundations underlying each intervention approach, extensive hands-on skill development with practice participants, and a detailed review of all protocol procedures. Competency assessment requires therapists to achieve a minimum score of 90% on written examinations covering theoretical knowledge and protocol specifications and satisfactory performance on practical skills assessments evaluated by master trainers. Weekly refresher sessions throughout the trial will maintain intervention quality, address emerging questions, and ensure continued protocol adherence.

To enhance baseline comparability across sites, participation is restricted to therapists possessing at least 5 years of stroke-specific rehabilitation experience. This requirement ensures foundational clinical expertise while creating greater homogeneity in health care provider characteristics. Each therapist will exclusively deliver 1 intervention type throughout the study, eliminating within-center variability and reducing contamination risk between treatment arms. The same therapist will treat all participants within their assigned center, maintaining consistency in intervention delivery style and therapeutic relationship development.

Structured peer observations using standardized feedback forms will maintain consistent intervention quality across sites. Detailed session plans specifying exercise sequences, progression criteria, and acceptable modifications will limit unwanted variability while preserving necessary clinical flexibility for individual participant needs. This comprehensive standardization approach minimizes therapist-related variability while enabling appropriate statistical control for unavoidable health care provider effects, strengthening our trial’s internal validity and interpretability.

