All participating centers will receive identical therapy kits containing standardized materials to eliminate equipment-related variability. We have developed a comprehensive therapy manual featuring detailed photographic demonstrations, step-by-step instructions, and decision algorithms guiding exercise selection and progression. We will systematically review individual participant progress in weekly case discussions and ensure protocol adherence while maintaining necessary clinical flexibility within our structured therapeutic framework.

The principal researcher and health care professionals will administer therapy sessions in all groups. To ensure rigorous data collection and participant safety, all participants will have standardized logbooks to document their therapy sessions. The research team will monitor each participant’s adherence to the assigned intervention and track any potential adverse events, such as muscle cramps or soreness, every week.

For participants with cognitive or motor limitations that affect their ability to maintain the logbooks independently, assistance will be provided by caregivers or trained research assistants. All instances of such assistance will be carefully recorded to preserve data integrity and allow for appropriate analysis and interpretation of the results.

This multimodal monitoring approach, incorporating both self-report and direct observation, is designed to comprehensively assess adherence while accommodating the potential functional limitations of the stroke survivor population. By systematically tracking adherence and adverse events, the study aims to ensure participant safety, maximize data quality, and ultimately enhance the validity and generalizability of the findings.

Table 2 outlines the framework of all study interventions, including a comparison between the 3 groups.

**Table 2 table2:** Framework of interventions: comparison between groups.

Characteristics	CIMT^a^ group	CIMT+NMES^b^ group	Control group
Total duration (min)	60	CIMT: 60; NMES: 20	60
Delivery	Researchers and health care professionals	Researchers and health care professionals	Researchers and health care professionals
Content	6 tasks of CIMT (50 repetitions for each task)	6 tasks of CIMT (50 repetitions for each task) + biofeedback electrical stimulator	Neurodevelopmental techniques emphasizing the functional task practice
Location	1 NASAM^c^ center	1 NASAM center	1 NASAM center

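### The therapist training, as written, gives every therapist the details of the other arms that the Blinding section says will be withheld, and opens a provider route for contamination

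*Protocol article*

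**What the plan says.** Recruitment and Randomization gives several grounds for assigning whole centers. Individual randomization within a center is called impractical. Clustering is then justified by contamination among patients: "A cluster randomization approach will be used to minimize contamination among patients attending the same center". It is justified again by contamination between arms: "to minimize the risk of contamination between intervention groups, a cluster randomization approach will be used". The same paragraph ends by stressing that contamination matters particularly for behavioral therapies delivered by providers. Three centers are used, one per arm.

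The Blinding section accepts that therapists cannot be blinded to their own treatment but limits what they learn about the rest of the trial. They are told that other modalities are under study at other centers, but "no particular details about the treatment regimens or locations will be provided". They are also "reminded not to disclose this information to other therapists, either within or at different centers".

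Therapist Training and Standardization requires every participating therapist to complete a 3-day program before treating anyone. Its single standardized curriculum covers "theoretical foundations underlying each intervention approach, extensive hands-on skill development with practice participants, and a detailed review of all protocol procedures". Therapists must score at least 90% on written examinations that include the specifications of the protocol, and refresher sessions follow every week. On quality control the section adds: "Structured peer observations using standardized feedback forms will maintain consistent intervention quality across sites". On staffing it says: "The same therapist will treat all participants within their assigned center". It also restricts each therapist to delivering one intervention.

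At the end of the Control Group section the protocol states: "All participating centers will receive identical therapy kits containing standardized materials to eliminate equipment-related variability".

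**The concern.** The Blinding section makes a promise about therapists' knowledge, and the training section describes a program that appears to break it. If the training is delivered as written, the control-center therapist will have studied the CIMT approach, reviewed its procedures and been examined on protocol specifications before treating the first control participant.

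Two things are at stake. First, the statement in the Blinding section would be untrue of the trial as conducted, and the final report would repeat it. Second, assigning one center per arm is a costly design, and the protocol lists it as a limitation. Protection against contamination is part of what the design is meant to buy. A control therapist who knows the CIMT protocol can, without intending to, bring parts of it into control sessions. That would shrink the difference between CIMT and control.

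**Working it through.** No arithmetic applies, so the check sets the passages side by side.

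1. **What must be withheld.** Under Blinding, therapists receive no details of regimens at other centers.

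2. **What those regimens are.** Three centers and three arms, with one center per arm, mean that the regimens at other centers are exactly the other two arms' interventions.

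3. **What is taught.** The curriculum is described as one standardized program for all participating therapists. Theory alone might not disclose a regimen. A detailed review of all protocol procedures, followed by an examination on protocol specifications, would. For CIMT those specifications include the six shaping tasks, the 300 repetitions per session and the mitt-wearing rule.

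4. **Whether any text limits the training by arm.** None does. The restriction to one intervention governs what a therapist delivers, not what a therapist is taught. The words *each* and *all* in the curriculum description point to common training.

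5. **Result.** From steps 1 to 4, a therapist trained literally as described has details of the other regimens. The rule on locations is not affected, because the training need not reveal which center runs which arm.

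6. **Whether there is a route into control sessions.** The Control Group section gives 20 of the 60 minutes to functional task practice aimed at activities of daily living. The CIMT tasks (lifting a cup, writing, moving a pen, putting on shoes) are also everyday activities. A route therefore exists. The length of this block is not an estimate of leakage.

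7. **What stands in the way.** Participants are to receive only their center's assigned intervention. Session plans fix exercise sequences, progression and permitted modifications. Intervention Fidelity Monitoring adds arm-specific checklists for every session, observation by the coordinator every two weeks, independent audit of 20% of sessions and one video-recorded session per therapist each week. These act on delivery and would catch gross departures. They do not change what the therapist knows.

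8. **Direction of any effect.** CIMT elements entering control sessions would move the control arm toward the two CIMT arms. The comparisons with control would be diluted. The comparison of CIMT plus NMES with CIMT alone would be largely unaffected by that route.

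**The case against.** The strongest reply is that the conflict is one of drafting. A curriculum can cover all three approaches without every therapist taking every part, and arm-specific delivery would fit both the Blinding section and the one-intervention rule. A condensed article may leave the allocation of modules to a training manual. This has some force: the intention may well be arm-specific. It does not settle the matter, because the published text describes one program for all therapists and says nothing of modules.

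A second reply is that knowledge is not delivery. Constraint for 90% of waking hours and 300 repetitions an hour could hardly slip unnoticed into a structured control session, and therapists with at least five years of stroke experience may already know CIMT. This stands as a reason to rate the risk as modest. It does not make the Blinding statement true.

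A third reply is that contamination between arms is only one of the reasons for clustering, and that protection against contact among patients is untouched by training. That is correct, which is why the point concerns the provider route only.

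Three stronger readings are tempting and are not supported:

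- **Kits.** A reader might infer that the identical kits put mitts, stimulators or the shaping-task instructions in the control center. The contents are not listed, and the sentence closes the Control Group section.
- **Peer observation.** A reader might infer that observers must come from another arm, since one therapist treats everyone at a center. The protocol does not say who observes whom. The non-disclosure rule mentions other therapists at the same center, and Table 2 lists researchers and health care professionals as delivering therapy, so same-center peers are possible.
- **Loss of power.** A reader might want to express the dilution as lost power. The protocol gives no leakage rate, so any such figure would rest on an invented one.

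**Conclusion.** The point holds in a limited form. On a literal reading, the training and examination described for all therapists contradict the Blinding section's statement about what therapists will know. They also open a provider route for contamination that the cluster design was partly meant to limit. This rests on reading the curriculum as common to all therapists, which is what the text says; if training is in fact arm-specific, the main conflict disappears once that is stated.

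The size of any dilution is unknown. Its likely direction is toward no difference in the comparisons with control. Contamination is a possibility opened by the plan, not something shown to occur, and the delivery safeguards reduce it. The change is worth making because it is cheap and removes the contradiction.

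**What to change.** - **Therapist Training and Standardization:** state that each therapist is trained, examined and refreshed only on the module for their own arm, plus procedures common to the whole trial such as logbooks and adverse event recording.
- **Peer observation, same section:** state that it takes place only within a center or arm. Alternatively, drop it and rely on the coordinator observations and independent audits already planned under Intervention Fidelity Monitoring.
- **Kits and manual, end of the Control Group section:** state that these are identical only for common materials and are otherwise arm-specific.

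The Blinding section can then stand as written.

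The cost is dividing the training and manual material by arm, holding separate training sessions, and having less peer feedback across sites. No extra staff or participants are needed.
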